Despite these advantages, rapid access to HF-MRI is often limited by the presence of contraindications or by its unavailability, especially in small hospitals and at night.^3^ Indeed, installing 1.5T or 3T MRI scanners is expensive and very demanding for the infrastructure and it requires continuous maintenance, sophisticated siting and utilisation. A low-field (LF) MRI scanner could operate in a broader range of environments, such as the emergency department (ED) or the ambulance setting (mobile stroke unit, MSU). Very recently portable LF-MRI has been evaluated in critically ill patients and resulted able to detect several types of brain injury, including ischaemic stroke, ICH, subarachnoid haemorrhage, traumatic brain injury and brain tumours.^11^ A preliminary study conducted in the intensive care unit setting demonstrated also an acceptable mean examination time (about 35 min) to deliver a complete protocol of diagnostic-grade sequences (T1W, T2W, T2, FLAIR, DWI).^12^ As for ischaemic stroke, performing DWI at 64 mT (Hyperfine LF-MRI, Guilford, Connecticut, USA) has been shown to successfully identify early lesions.^11^,^13^ Furthermore, LF-MRI DWI and FLAIR sequences were able to detect infarcts as small as 4 mm in diameter in >90% patients across cortical, subcortical and cerebellar structures, showing a strong correlation between ischaemic volumes, stroke severity and functional outcomes at the discharge.^14^

Referring to ICH, LF-MRI was evaluated mostly in the subacute phase, therefore, data on the hyperacute assessment are largely missing.^15^ Interrater discordance among expert neuroradiologists was observed mainly in detecting small haematomas, especially located in the posterior fossa.^15^ Potential advantages and current limitation of LF-MRI in acute stroke are reported in box 1.

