### Study design

The Point-of-care low-field MRI in acute Stroke study is a multicentric, prospective clinical trial involving adult patients with suspected stroke. Recruitment of patients will be performed at three study units: Azienda Sanitaria Locale (ASL) Abruzzo 1, Hospitals of L’Aquila and Avezzano, Italy (ASLAQ); ASL Abruzzo 2, Hospital of Chieti, Italy (ASLCH); Istituto di Ricerca e Cura a Carattere Scientifico (IRCCS) Humanitas Research Hospital of Milan, Italy (HUM). Additional units contributing to the study will include:

University of L’Aquila (UNIVAQ) will be in charge of study coordination, data analysis and management, optimisation of LF-MRI protocols, and cost-effectiveness assessment of LF-MRI within the Italian public care system.Marche Polytechnic University (UNIPM) will perform independent assessment and adjudication of anonymised clinical, LF-MRI and conventional neuroimaging data in a blinded fashion; it will also identify the best possible treatment option for patients with suspected ischaemic stroke (IVT, EVT, combined revascularisation treatment, no revascularisation).‘G. Martino’ Polyclinic University Hospital (POLIME) will perform blinded and independent assessment and adjudication of anonymised clinical and conventional neuroimaging data, also will identify the best possible treatment option for patients with suspected ischaemic stroke and provide historical HF-MRI data of patients with stroke to be used for AI algorithms training.Free University of Bozen-Bolzano (UNIBZ) will develop and optimise AI algorithms suitable for LF-MRI images interpretation starting from anonymised conventional HF-MRI and LF-MRI data provided by ASLAQ, ASLCH, HUM and POLIME.University of Cassino and Southern Lazio (UNICAS) will perform a feasibility study to develop an ambulance (MSU) equipped with an LF-MRI scanner.

Agreement with conventional neuroimaging will be evaluated at different time points (hyperacute, acute—24 hours, subacute—72 hours, discharge, chronic—4 weeks) by ASLAQ, ASLCH, HUM, POLIPM and POLIME. At each time point, LF-MRI will be scheduled immediately after conventional neuroimaging to ensure comparability between performed investigations. In summary, this trial will provide necessary data to validate the use of LF-MRI in the acute stroke healthcare system.

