Patients with suspected acute stroke will undergo diagnostic procedures and management according to usual clinical care. LF-MRI will be performed on admission, 24 hours, 72 hours, at the hospital discharge and 4 weeks after the event. LF-MRI findings will not be used to make clinical decisions on patients’ management. Every time a stroke dispatch is activated, the dedicated research staff will be alerted by the local neurologist on duty. The research staff will check eligibility criteria, obtain informed consent and perform study procedures independently of the personnel in charge of managing the acute stroke case. All included patients with suspected stroke will be managed and treated per usual care by the hospital staff not involved in study procedures. Conventional stroke imaging will be performed as needed according to current clinical practice (non-contrast CT+CT angiography and/or HF-MRI+MRI angiography in selected cases, with/without CT or HF-MRI perfusion study).

For the aim of the study, all included patients will be investigated with LF-MRI at predefined time points (24 hours, 72 hours, hospital discharge, 4 weeks). The acquisition of LF-MRI will be performed by a dedicated study staff that will be distinct from the clinical staff involved in the care of the acute stroke patient, thus not subtracting time or resources to usual care. Information obtained by LF-MRI will not be used to take clinical decisions regarding further investigations or treatment. Due to feasibility reasons, the study will include only patients presenting to the ED with suspected stroke during weekdays daytime hours. Study procedures are summarised in figure 1.

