### Time points and collected variables

The following clinical variables will be collected at the specified time point:

Hyperacute (ED): demographical data, time from symptom onset (precise onset, unwitnessed, wake-up stroke), onset-to-door-time, door-to-imaging time, clinical severity (National Institute of Health Stroke Scale, NIHSS), type of neuroimaging, duration of LF-MRI scanning, conventional neuroimaging and LF-MRI findings (detection of ischaemic or haemorrhagic lesion(s), lesion(s) number, location and volume, detection and characteristics of possible LVO, collateral flow assessment, Alberta Stroke Programme early CT score^16^ and/or DWI/FLAIR mismatch for MR, pre-EVT grade of perfusion according to the thrombolysis in cerebral infarction—TICI—scale), treatment decision (IVT, EVT, IVT+EVT, none), time (door-to-needle for IVT and door-to-groin for EVT), clinical outcome (NIHSS score immediately after IVT/EVT—if performed) and reperfusion outcome (TICI score immediately after EVT—if performed).Acute (24 hours) and subacute (72 hours): clinical severity (NIHSS), conventional neuroimaging type and findings, LF-MRI findings (lesion volume and characteristics, evolution—for example, presence and entity of haemorrhagic transformation).Hospital discharge: days of hospital stay, functional outcome at discharge (modified Rankin scale), final adjudication of the event (ischaemic stroke, ICH, SAH or mimic), assessment of aetiology according to the Trial of ORG 10172 in Acute Stroke Treatment (TOAST) classification^17^—for ischaemic stroke.Chronic (4 weeks): conventional neuroimaging type and findings, LF-MRI findings (lesion volume, characteristics and evolution), assessment of stroke aetiology (TOAST)^17^ also considering findings from postdischarge clinical investigations.

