Detection of lesions at LF-MRI versus non-contrast CT: to compare the accuracy of LF-MRI scans with the accuracy of routinely performed head CT scans for infarcts and haemorrhage detection (endpoint: agreement between LF-MRI and head CT scans in detecting infarcts and haemorrhages).Detection of lesions at LF-MRI versus HF-MRI: to compare the accuracy of LF-MRI scans with the accuracy of routinely performed brain HF-MRI scans for infarcts and haemorrhage detection (endpoint: agreement between LF-MRI and HF-MRI scans in detecting infarcts and haemorrhages).Treatment decision-making based on LF-MRI: to evaluate the impact of LF-MRI on the clinical decision-making process related to revascularisation treatments for ischaemic stroke, as compared with the conventional acute stroke diagnostic (endpoint: agreement between the best treatment option based on LF-MRI and the best treatment option based on conventional imaging).Impact of LF-MRI implementation on the door-to-needle time (DTNT) in patients eligible to IVT: to evaluate whether the implementation of LF-MRI may impact on the DTNT in patients treated with IVT at each recruiting site (endpoint: comparison between the mean DTNT recorded during the 2 months before the protocol initiation—and in patients who refuse to undergo LF-MRI during the study period—and the mean DTNT estimated basing on the results of LF-MRI).Early identification of stroke mimics with LF-MRI: to assess whether LF-MRI may improve the detection of patients with stroke mimics in the acute phase and the discrimination with acute ischaemic stroke (endpoint: agreement between LF-MRI and conventional imaging in detecting stroke mimics).Agreement between LF-MRI and conventional brain imaging at different post-stroke time points: to assess the performance of LF-MRI at different phases of the ischaemic stroke process (hyperacute, acute—24 hours, subacute—72 hours and chronic—4 weeks from the event) and to compare with findings from conventional neuroimaging (endpoint: agreement between LF-MRI and conventional neuroimaging at different stroke phases).

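### LF-MRI is done in every patient but its conventional comparator only where usual care obtains one, so the HF-MRI and phase-by-phase kappas describe an undefined paired subset and are at risk of selection bias

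*Protocol article*

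**What the plan says.** The Study design section gives the two imaging streams different rules. For the comparator: "Conventional stroke imaging will be performed as needed according to current clinical practice". The bracket that follows lists CT with CT angiography "and/or HF-MRI+MRI angiography in selected cases". For the index test: "all included patients will be investigated with LF-MRI at predefined time points".

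Other statements presume that the comparator is there. Study design also says: "At each time point, LF-MRI will be scheduled immediately after conventional neuroimaging to ensure comparability between performed investigations". The section on time points and collected variables lists, for 24 and 72 hours, "clinical severity (NIHSS), conventional neuroimaging type and findings, LF-MRI findings" and, later, "Chronic (4 weeks): conventional neuroimaging type and findings, LF-MRI findings".

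Outcomes measurement then sets secondary endpoints on these comparisons. One is "agreement between LF-MRI and HF-MRI scans in detecting infarcts and haemorrhages". Another is agreement with conventional imaging in the hyperacute phase, at 24 hours, at 72 hours and at 4 weeks. The Statistical plan analyses agreement with Cohen's kappa.

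**The concern.** A kappa needs both scans in the same patient. If clinicians decide who gets the comparator, the patients with a pair may not resemble those enrolled. At admission they could be the patients with an unclear CT. The Introduction also says that "rapid access to HF-MRI is often limited by the presence of contraindications or by its unavailability", so some patients cannot contribute to the HF-MRI comparison at all. Box 1 names some such patients (agitated, critically ill, with implanted devices) among those for whom LF-MRI is meant to extend imaging. At later time points, the patients re-imaged could be those who deteriorated or were treated.

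Two conclusions are at stake. The HF-MRI kappa could be read as LF-MRI performance in the enrolled population when it describes a subset. A rise or fall in kappa from the hyperacute phase to 4 weeks could be read as a property of LF-MRI when it comes from a change in who was scanned.

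**Working it through.** **1. The statements side by side.** No statement in the article requires an HF-MRI, or a follow-up conventional scan, for study purposes. The rule tied to usual care has no exception for later phases. The scheduling sentence and the variable list assume a conventional scan at 24 hours, 72 hours and 4 weeks. Discharge is also unsettled: Study design names it as an agreement time point, but the variables listed for discharge contain no imaging and the phase endpoint omits it. The text therefore does not settle which pairs will exist.

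**2. How many pairs the plan counts on.** Sample size calculation gives n=214 for agreement: kappa 0.8, outcome about 20%, power 80%, about 10% dropout. The null kappa is not stated; I assume 0.6 and two-sided alpha 0.05. The goodness-of-fit method for a binary kappa uses the cell probabilities π²+π(1−π)κ, 2π(1−π)(1−κ) and (1−π)²+π(1−π)κ.
- At κ=0.6: 0.136, 0.128, 0.736. At κ=0.8: 0.168, 0.064, 0.768.
- Σ(difference²/null) = 0.032²/0.136 + 0.064²/0.128 + 0.032²/0.736 = 0.0409.
- n = (1.96+0.84)²/0.0409 = 7.849/0.0409 ≈ 192 pairs; 191.8/0.9 = 213.1, rounded up to 214. The stated figure is reproduced.

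Of 300 enrolled, 270 remain after 10% loss. The HF-MRI comparison reaches 192 pairs only if 192/270 = 71% of patients have HF-MRI. The article does not give that share. For κ=0.8 and outcome 20%, the variance factor is 0.2×[0.2×(−0.6) + 0.96/0.32] = 0.576, so the 95% half-width is 1.96×√(0.576/n).

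| Share with HF-MRI (assumed) | Pairs of 270 | Half-width | Approximate power against 0.6 |
|---|---|---|---|
| 10% | 27 | 0.29 | 18% |
| 20% | 54 | 0.20 | 32% |
| 30% | 81 | 0.17 | 44% |
| 50% | 135 | 0.13 | 65% |
| 100% | 270 | 0.09 | 91% |

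**3. What selection could do to kappa.** From Sample size calculation: sensitivity 0.90, specificity 0.80, stroke prevalence 0.80. Everything else is assumed: HF-MRI makes no errors, and half the strokes are easy to see (LF-MRI sensitivity 0.98) and half hard (0.82). Ischaemic and haemorrhagic strokes are pooled as the target, so no separate infarct prevalence enters.

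In the full population, observed agreement is 0.72+0.16 = 0.88, chance agreement is 0.76×0.80+0.24×0.20 = 0.656, and kappa = 0.224/0.344 = 0.65.

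| Assumed HF-MRI ordering: easy / hard / mimic | Pairs of 270 | Prevalence in pairs | Sensitivity in pairs | Kappa |
|---|---|---|---|---|
| 30% / 30% / 30% | 81 | 0.80 | 0.90 | 0.65 |
| 20% / 60% / 20% | 97 | 0.89 | 0.86 | 0.47 |
| 60% / 60% / 20% | 140 | 0.92 | 0.90 | 0.48 |
| 60% / 20% / 20% | 97 | 0.89 | 0.94 | 0.66 |
| 30% / 30% / 80% | 108 | 0.60 | 0.90 | 0.71 |

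In the third row, sensitivity and specificity do not change; kappa falls because the mix of strokes and mimics does. Comparing the second and fourth rows, kappa would appear to rise from 0.47 to 0.66 between two phases if hard strokes were imaged preferentially at one and easy strokes at the other, with the same scanner and the same readers.

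**4. The same for infarcts alone.** Infarct prevalence 0.80×0.71 = 0.568 (71% is the ischaemic share in the Introduction); other strokes 0.232; mimics 0.20. Haemorrhages are counted as CT-positive, because the Introduction puts CT accuracy for intracerebral haemorrhage at about 100%. Assumed: CT shows 45% of infarcts; LF-MRI detects 98% of CT-visible and 75% of CT-occult infarcts, with 10% false positives; HF-MRI is error-free and is done in 10% of CT-positive and 60% of CT-negative patients.
- All patients: detection 0.45×0.98+0.55×0.75 = 0.85, kappa 0.75.
- Pairs: 0.0256+0.1874+0.0232+0.12 = 0.356 of 270, or 96 patients; detection (0.0256×0.98+0.1874×0.75)/0.213 = 0.78, kappa 0.65.
- If haemorrhages are instead counted as CT-negative: about 127 patients, kappa 0.68.
- Equal ordering rates: kappa stays at 0.75.

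**The case against.** **The HF-MRI endpoint is already conditional.** Outcomes measurement speaks of routinely performed HF-MRI and does not claim one in every patient. A kappa in patients with both scans is a legitimate quantity. This stands, and it is why the repair is a matter of definition. But the Objectives section states the comparison with CT and HF-MRI without that limit, and nothing confines the conclusion to paired patients.

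**LF-MRI does not drive the ordering.** Study design keeps LF-MRI findings out of decisions on further investigations, so the classic form of partial verification, in which the index test selects who is verified, is excluded. This stands. Selection through CT findings, clinical course or contraindications remains possible.

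**Follow-up scans may be planned.** The sentence on usual care sits in the description of the acute work-up, and the figure of study procedures is not available here. A reader might infer that follow-up conventional scans exist only where clinicians order them. The article does not establish that; it is inconsistent on the matter.

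**Bias is not shown.** A reader might infer that these kappas are biased. Equal ordering gives no bias, and the assumed patterns move kappa both ways. Only a risk is supported.

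**Corrections may be in the analysis plan.** That plan is not shown, so the lack of a correction method is not the point. The contradictory statements and the undefined population are in the article itself.

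**Weighting has limits.** Patients with an HF-MRI contraindication have no chance of a pair and cannot be recovered by weighting. With 10% verified in a stratum, weights reach 10. This argues for a sensitivity analysis, not for a weighted main result.

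**Conclusion.** The point holds for the HF-MRI agreement endpoint and the later-phase agreement endpoint, both secondary. As written, their raw kappas describe only patients with a paired scan, a set that may differ from the enrolled population and from phase to phase. They carry a risk of selection bias of unknown size and direction, and a contrast between phases can be confounded by who was re-imaged. The statements on follow-up conventional imaging contradict each other and must be reconciled.

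The range of 0.47 to 0.71 around 0.65 is an illustration. It rests on assumed ordering rates, an assumed split into easy and hard strokes, and an error-free HF-MRI; it is not a forecast. The pair counts and power rest on an assumed HF-MRI share and an assumed null kappa of 0.6. They do not show that 214 is wrong: that figure is for conventional imaging in general and reproduces. They show only that its stated allowance covers dropout and not absent comparators.

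The primary endpoint is judged against final adjudication and is outside this point.

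**What to change.** 1. Reconcile the statements in Study design and in the section on time points and variables, so that it is clear which conventional scans are expected at each time point, discharge included.
2. Define the HF-MRI and later-phase endpoints as agreement among patients with a paired scan, and limit the conclusion to them.
3. Report, for each comparison and phase, the number and baseline characteristics of patients with and without a pair.
4. Make any contrast between phases within patients who have pairs at both phases.
5. Beside the raw kappa, add a verification-corrected estimate as a sensitivity analysis (inverse-probability weighting or Begg-Greenes), with verification modelled on the LF-MRI result, admission CT, NIHSS, onset time and treatment. Limit it to patients who could have had the comparator.

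The cost is some wording, one table and one additional model, best settled before agreement results are seen. No extra scans and no change to care are needed. The sensitivity analysis will have wider intervals, possibly much wider where few patients are verified, and it assumes that scans are missing at random given the modelled variables. Restricting phase contrasts to patients paired at both phases also reduces their number.

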**Figure 1 F1:**
[figure not shown]
Study units and procedures of the POCS protocol. ASLAQ, ASL Abruzzo 1 (Hospitals of L’Aquila and Avezzano); ASLCH, ASL Abruzzo 2 (Hospital of Chieti); ED, emergency department; EVT, endovascular treatment; HF, high-field; HUM, Humanitas Research Hospital; IVT, intravenous thrombolysis; LF, low-field; MSU, mobile stroke unit; POCS, point-of-care low-field MRI in acute stroke; POLIME, ‘G. Martino’ Polyclinic University Hospital; UNIBZ, Free University of Bozen-Bolzano; UNICAS, University of Cassino and Southern Lazio; UNIPM, Marche Polytechnic University; UNIVAQ, University of L’Aquila.

### Study population, inclusion and exclusion criteria

The study will include consecutive patients admitted to the ED of recruiting centres with a dispatch of suspected stroke. Dispatches will be provided by Emergency Medical Services or ED physicians according to local acute stroke management protocols and current clinical practice.

Inclusion criteria are the followings: (1) symptoms suggestive of acute stroke (acute onset of a focal neurological deficit which can be referred to the involvement of a specific CNS region); (2) stroke onset <24 hours since when the patient was last known healthy; (3) age ≥18 years and (4) written informed consent provided by the patient himself or by proxy (for unconscious patients, cognitively impaired or aphasic).

Patients meeting at least one of the following criteria will be excluded from the study: (1) symptoms not indicative of acute stroke (eg, syncope, tonic or clonic activity, dizziness or wooziness alone, confusion and amnesia alone, subacute or chronic development of a focal neurological deficit); (2) inability to undergo LF-MRI due to critically impaired vital functions (eg, haemodynamically unstable patients, need of immediate life-saving manoeuvres); (3) implanted ferromagnetic devices potentially interfering with LF-MRI (eg, cochlear implants) and (4) impossibility to achieve written informed consent.

### LF-MRI equipment and imaging protocol

Three FDA and EU approved portable LF-MRI commercialised by Hyperfine Research (www.hyperfine.io) will be employed. All patients will be preliminarily tested with a metal detector to ensure the absence of potentially interfering ferromagnetic devices throughout the body. Patients will undergo LF-MRI directly in the CT suite during the downtime of preparation which usually occurs after urgent CT imaging (current mean door-to-imaging time: **~**20–25 min), thus not delaying the conventional diagnostic process and treatment administration. Specifically, LF-MRI acquisition will be performed during the time needed to obtain the neuroradiological report, waiting for results of essential laboratory tests, stroke nurse arrival, IVT initiation and/or preparation of the angiography room. For patients eligible for immediate IVT following brain CT, LF-MRI will be conducted simultaneously during the administration of IVT. In cases where acquisition of images with LF-MRI is supposed to delay initiation of revascularisation procedures, study procedures will be stopped and the patient will be excluded from the study. LF-MRI will also be repeated by the study staff at predefined time points: 24 hours, 72 hours, at the discharge and 4 weeks after the event.

A prespecified acquisition of Fast-Spin Echo essential stroke sequences will be performed, starting with DWI, apparent diffusion coefficient (ADC) mapping and FLAIR. Other sequences will be performed based on DWI (ADC) and FLAIR findings and on clinical information (suspected stroke subtypes, eligibility to reperfusion treatment), to shorten the duration of LF-MRI acquisition and avoid treatment delay. The prespecified LF-MRI minimum acquisition time pulse sequences protocol is displayed in figure 2. Furthermore, an angiographic sequence will be tested to assess the presence of cerebral LVO or stenosis. This sequence will evaluate the loss of signal due to blood flow in the time frame between the excitation pulse and signal refocusing. Overall, LF-MRI acquisition has been set up to require ~20–25 min to complete, as estimated using the Hyperfine model of portable LF-MRI.

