### Outcomes measurement

All events will be adjudicated as ischaemic stroke, ICH, SAH or stroke mimic. For each of the three recruiting units a senior neurologist and a neuroradiologist will adjudicate clinical data and neuroimaging findings at LF-MRI. A different pair of senior neurologist and neuroradiologist will adjudicate events based on clinical data and conventional neuroimaging. The pair assessing LF-MRI will be blinded to findings of conventional neuroimaging and vice-versa. All included patients will be independently adjudicated for variables of interest by the study staff of UNIPM or POLIME: UNIPM will adjudicate clinical and LF-MRI findings; POLIME will adjudicate clinical and conventional neuroimaging findings. In case of disagreements, final adjudication will be performed by the principal investigator of the study. UNIPM will identify the best possible treatment option for patients with ischaemic stroke based on LF-MRI, while POLIME will identify treatment options based on conventional imaging.

This study has a primary outcome and a number of cosecondary outcomes. The primary outcome measure of the study is the accuracy of LF-MRI in the diagnosis of stroke in the acute phase (endpoint: sensitivity and specificity with respect to final adjudication of the event). Secondary outcome measures include:

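### Patients in whom LF-MRI is expected to delay revascularisation are dropped from the study itself, so accuracy and treatment agreement are estimated only where the scan fitted the pathway

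*Protocol article*

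**What the plan says.** The rule stands in the protocol article under *LF-MRI equipment and imaging protocol*. Its trigger is "In cases where acquisition of images with LF-MRI is supposed to delay initiation of revascularisation procedures"; its consequence is that "study procedures will be stopped and the patient will be excluded from the study". The patient leaves the study, not only the scan.

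Four other statements bear on it:

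- *Study design* gives the order of events: "The research staff will check eligibility criteria, obtain informed consent and perform study procedures independently of the personnel in charge". Stopping study procedures therefore normally comes after eligibility has been checked and consent obtained.
- *Study population, inclusion and exclusion criteria* describes the series: "The study will include consecutive patients admitted to the ED of recruiting centres with a dispatch of suspected stroke". It lists four exclusion criteria. Expected delay to revascularisation is not one of them.
- The imaging section limits who can be affected: "For patients eligible for immediate IVT following brain CT, LF-MRI will be conducted simultaneously during the administration of IVT". It also places scanning in waiting time after CT, such as the wait for laboratory results or for the angiography room.
- The same section gives the scan length: "LF-MRI acquisition has been set up to require ~20–25 min to complete".

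Under *Outcomes measurement*, "The primary outcome measure of the study is the accuracy of LF-MRI in the diagnosis of stroke in the acute phase", with sensitivity and specificity judged against the final adjudication. Secondary endpoints include agreement between the treatment options chosen from LF-MRI and from conventional imaging, and door-to-needle time (DTNT), the aim there being "to evaluate whether the implementation of LF-MRI may impact on the DTNT in patients treated with IVT at each recruiting site".

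**The concern.** A test that cannot be completed in time cannot guide the treatment decision, and guiding that decision is the second stated objective. Under this rule such cases do not count as a limitation of LF-MRI. They disappear from the denominator, and the trigger is the index test itself.

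The loss is also selective. Only patients heading for revascularisation can trigger the rule. Haemorrhages, strokes not treated by revascularisation, and mimics not selected for it cannot. The treatment-agreement endpoint therefore loses patients from the very group it is about.

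The trigger is an expectation of delay, judged case by case at three recruiting units, and the article gives no criterion for it. The excluded share could differ between units for reasons unrelated to the patients.

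The article does not say that removed patients are counted, adjudicated, or brought back for the 24-hour, 72-hour, discharge and 4-week scans. Read literally, those data are lost too.

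**Working it through.** **Step 1: the plan's own figure.** There is none to reproduce. The article gives no expected number of delay exclusions and does not say whether they fall within its dropout allowance of about 10%.

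**Step 2: who can be removed.** Removal requires that (a) the patient is a revascularisation candidate, (b) the patient is not covered by scanning during thrombolysis, and (c) the remaining preparation time is shorter than about 20–25 min. This leaves a residual group, probably mainly candidates for endovascular treatment. The documents give no size for it.

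**Step 3: effect on sensitivity.** Inputs from *Sample size calculation*: LF-MRI sensitivity 0.90, stroke prevalence 0.80, N = 300, so 300 × 0.80 = 240 strokes before dropout. Assumed: a share f of all strokes is removed, and LF-MRI would have had sensitivity Se_x in them.

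Full-cohort sensitivity = (1 − f) × 0.90 + f × Se_x

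| Removed strokes treated as | f = 5% (12 of 240) | f = 10% (24) | f = 20% (48) |
|---|---|---|---|
| Se_x = 1.00 | 0.905 | 0.910 | 0.920 |
| Se_x = 0.90 | 0.900 | 0.900 | 0.900 |
| Se_x = 0.70 | 0.890 | 0.880 | 0.860 |
| Se_x = 0.50 | 0.880 | 0.860 | 0.820 |
| No diagnosis (intention to diagnose) | 0.855 | 0.810 | 0.720 |

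Example: 0.95 × 0.90 = 0.855; 0.90 × 0.90 = 0.810.

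The first four rows concern image reading, and there the sign depends on Se_x. The last row asks whether LF-MRI delivered a correct diagnosis in time. On that question the completed-scan figure is always too favourable, by f × 0.90. Because f is a share of all strokes and only candidates can be removed, a given f means a larger share of candidates; 20% is shown only to mark out the range.

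**Step 4: precision.** Half-width = 1.96 × √(0.90 × 0.10 / n). With n = 240 it is 3.8 points. With 10% removed, n = 216 and it is 4.0 points. The issue is selection, not power.

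**Step 5: mean DTNT.** Two effects oppose each other; all values of f and of the differences are assumed.

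- If 10% of thrombolysed patients are removed and a completed scan would have delayed each by 20–25 min, the delay left out of the mean is 0.10 × 20 = 2.0 to 0.10 × 25 = 2.5 min.
- If those 10% would have had a DTNT 20 min shorter than the rest, the retained mean is 0.10 × 20 = 2 min too long, which works against LF-MRI.

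The net direction cannot be derived. The article states no corresponding filter for the comparators (the two months before the study, and refusers).

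**The case against.** A reader might infer that the rule strips out the most urgent strokes and so makes LF-MRI look better on every endpoint. The documents do not support that, for four reasons.

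- Patients eligible for immediate thrombolysis are scanned during infusion and kept, and scanning otherwise uses existing waiting time. The group removed is narrower.
- Nothing in the article gives LF-MRI accuracy in those removed. Large, obvious lesions would mean that dropping them lowers measured sensitivity; very early, subtle ones would mean the opposite. The same holds for treatment agreement.
- The LF-MRI side of the DTNT endpoint is an estimated time, and LF-MRI does not guide care. Patients whose scan is stopped are treated as usual, so their observed DTNT would reveal no LF-MRI delay.
- Any exclusion rate is assumed, and scoring removed patients as failures measures feasibility together with accuracy, not reading skill.

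All four stand, and they limit the point. It can also be said that analysis sets and the handling of incomplete scans belong in a statistical analysis plan that is not shown. That is fair for the detail of the analysis. It does not answer the main point: the article already fixes removal from the study, and an analysis plan cannot restore patients whose adjudication and follow-up may never be collected.

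**Conclusion.** The point holds in a limited form. The article removes patients, normally after consent, for a reason created by the test under study. The rule is missing from the exclusion criteria and conflicts with the consecutive series. Accuracy and treatment agreement will describe only patients in whom LF-MRI fitted the pathway.

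This favours LF-MRI on feasibility and on intention-to-diagnose accuracy. For image-reading sensitivity, treatment agreement and mean DTNT the direction is unknown, and once the patients are gone neither size nor sign can be estimated.

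The size is illustrative only. At an assumed 5% or 10% of strokes affected, 90% on completed scans corresponds to 85.5% or 81.0% by intention to diagnose. This rests on the article's 90% planning value and on counting every scan not completed as no diagnosis. The safety stop itself is not questioned.

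**What to change.** 1. Leave the safety stop unchanged. Replace the removal of the patient with wording such as: *hyperacute LF-MRI recorded as not completed; patient stays in the study cohort*.
2. Reconcile the imaging section with the population section, so that the exclusion criteria and the consecutive series agree with what happens to these patients. State whether they continue with the later scans.
3. Report their number, treatment route and final adjudication, overall and by recruiting unit.
4. Give sensitivity, specificity and treatment agreement on completed scans and, alongside, an intention-to-diagnose analysis in which a hyperacute scan not completed counts as not correct (for treatment agreement, as no agreement).
5. Report the observed DTNT of these patients separately. Do not pool it into the LF-MRI-estimated mean, which is a different quantity.

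Cost: a short amendment, which under *Protocol amendments* needs approval by the funder and the ethics committees; a CRF field for a scan not completed; and slightly more data collection. Treatment decision, treatment times and final adjudication are already among the variables collected. Whether existing consent covers continued follow-up cannot be seen from the article and should be checked. The intention-to-diagnose figures will be less favourable than those on completed scans.
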